## Abstract

**Introduction:**

Severe Graves’ disease is a life-changing condition with poor outcomes from currently available treatments. It is caused by directly pathogenic thyroid-stimulating hormone receptor-stimulating antibodies (TRAb), which are secreted from plasma cells. The human anti-CD38 monoclonal antibody daratumumab was developed to target plasma cells which express high levels of CD38, and is currently licensed for treatment of the plasma cell malignancy, myeloma. However, it can also deplete benign plasma cells with the potential to reduce TRAb and alter the natural history of severe Graves’ disease. This study aims to establish proof of concept that daratumumab has efficacy in patients with severe Graves’ disease and will provide important data to inform a choice of dosing regimen for subsequent trials.

**Methods and analysis:**

The Graves-PCD trial aims to determine if daratumumab modulates the humoral immune response in patients with severe Graves’ disease, and if so, over what time period, and to find an optimal dose. It is a single-blinded, randomised, dose-finding, adaptive trial using four different doses of daratumumab or placebo in 30 adult patients. Part 1 of the trial is dose-finding and, following an interim analysis, in part 2, the remaining patients will be randomised between the chosen dose(s) from the interim analysis or placebo. The primary outcome is the percentage change in serum TRAb from baseline to 12 weeks.

**Ethics and dissemination:**

The trial received a favourable ethical opinion from London-Hampstead Research Ethics Committee (reference 21/LO/0449). The results of this trial will be disseminated at international meetings, in the peer-reviewed literature and through partner patient group newsletters and presentations at patient education events.

**Trial registration number:**

ISRCTN81162400.

STRENGTHS AND LIMITATIONS OF THIS STUDYCurrent treatments for patients with severe Graves’ disease are unsatisfactory and there is therefore significant unmet clinical need for new treatment.Adaptive design allows efficient investigation of multiple doses.The long-term remission of hyperthyroidism cannot be assessed in the 24-week follow-up period.The duration of treatment or dosing intervals will not be tested in this study.

## Introduction

Graves’ disease (autoimmune hyperthyroidism) affects around 3% of women and 0.5% of men, and most commonly presents in people in their 30s and 40s with a disproportionate burden of ill-health falling on working-age women.^1 2^ Typical symptoms include weight loss, palpitations, heat intolerance, tremor, breathlessness, sweating, insomnia, loss of concentration and irritability. Around 40% of patients develop thyroid eye disease (TED),^3^ which can cause facial disfigurement as well as functional visual problems and even loss of sight. Quality of life in patients with TED is poor, worse than for diabetes, and similar to patients with inflammatory bowel disease.^4^ Rarely, thyroid dermopathy (pretibial myxoedema) may also occur leading to a brawny thickening of the skin on the lower legs and feet.^5^ These latter two problems produce particularly distressing symptoms for a relatively young and active patient group. Around 10% of patients with Graves’ disease have a severe form of the disease, and experience severe thyrotoxicosis (serum FT4 ≥50 pmol/L (upper limit of reference range 22 pmol/L) or FT3 ≥15 pmol (upper limit of reference range 6.8 pmol/L)), failure of medical control of hyperthyroidism, large goitre, TED of sufficient severity to affect visual function or thyroid dermopathy. Current treatments for these patients with severe Graves’ disease give unsatisfactory outcomes and are expensive, typically involving surgical thyroidectomy with or without several episodes of eye surgery.^6^

Conventional treatment of Graves’ disease with antithyroid drugs (carbimazole, methimazole or propylthiouracil) leads to remission for only around 50% of patients, decreasing to less than 20% for patients with severe disease, and does not improve eye symptoms.^7 8^ Other treatment options of radioactive iodine or surgical thyroidectomy result in life-long hypothyroidism requiring levothyroxine therapy, which patients are often unwilling to accept.^9^ Better treatment options are sorely needed for severe Graves’ disease.

Severe Graves’ disease is caused by high titres of directly pathogenic thyroid-stimulating hormone (TSH) receptor-stimulating antibodies (TRAbs), which are secreted from terminally differentiated B lymphocytes known as plasma cells.^10^ Not only do TRAbs directly stimulate thyroid hormone overproduction (leading to hyperthyroidism), they also cause thyrocyte hyperplasia leading to goitre, and bind to TSH receptors on the surface of orbital fibroblasts leading to mitogenic signalling that triggers and perpetuates eye disease. Failure of medical control and/or early relapse following conventional antithyroid drugs reflects the persistence of these long-lived, TRAb-secreting plasma cells in the secondary lymphoid tissues and bone marrow.

Both benign and malignant plasma cells express high levels of the cell-surface glycoprotein CD38. Daratumumab, a biological drug that targets CD38, was recently licensed for the plasma cell malignancy, myeloma.^11 12^ This human anti-CD38 monoclonal antibody has the potential to deplete plasma cells and therefore produce a rapid reduction in TRAb levels, which may alter the natural history of severe Graves’ disease. This study aims to establish proof of concept that daratumumab has efficacy in patients with severe Graves’ disease and will provide important data to inform a choice of dosing regimen.

Tolbert *et al* first reported the use of daratumumab in the treatment of benign, antibody-mediated haematological autoimmune disorders in 2016.^13^ In this case, a female in her late teens with autoimmune haemolytic anaemia (post-stem cell transplant) was successfully treated with daratumumab and had an instant improvement in haemolysis. There are now numerous additional reports of daratumumab being repurposed to target benign disorders.^14–17^

Daratumumab is licensed for use in myeloma at a dose of 16 mg/kg; however, patients with Graves’ disease have several orders of magnitude fewer plasma cells and it is therefore expected that lower doses of drug will be active in this patient group with benign disease. To address this question, the first stage of the study will be dose-finding. Notably, dose-finding trials in patients with myeloma showed no difference in adverse event (AE) rates between doses of 8 mg/kg and 16 mg/kg, and no dose-limiting toxicity up to 24 mg/kg.^11^ Therefore, in order to define a signal for efficacy, this study will use 9 mg/kg as the top dose in stage 1, with reducing concentrations (3 mg/kg, 1 mg/kg and 0.5 mg/kg) along with placebo to determine the dose–response in stage 1. As myeloma trials did not find increased AEs or toxicities at higher doses, these four dose allocations will take place in parallel. Stage 2 of the study will randomise additional patients to one or more optimal doses of daratumumab, as selected from stage 1, or placebo to gain further information about real-life effect size, safety and tolerability.

## Methods and analysis

This study protocol is based on the Standard Protocol Items: Recommendations for Interventional Trials 2013 statement.^18^

### Sponsor and trial management

The trial sponsor is the Newcastle upon Tyne Hospitals NHS Foundation Trust (email: [contact]). Trial management is delegated to the Newcastle Clinical Trials Unit (NCTU), Newcastle University.

### Objectives

The primary objective is to determine if daratumumab modulates the humoral immune response in patients with severe Graves’ disease, with the primary outcome measure the percentage change in serum TRAb from baseline to 12 weeks. Secondary objectives include determining the optimal dose of daratumumab, assessing safety, patient quality of life and impact on eye symptoms, thyroid function and goitre size (see table 1).

**Table 1 T1:** Objectives and outcome measures

	Objectives	Outcome measures
Primary	To determine if daratumumab modulates the humoral immune response in patients with Graves’ disease	Change in serum TRAb from baseline to 12 weeks compared with change in placebo group
Secondary	To determine how fast daratumumab modulates the humoral immune response in patients with Graves’ disease	Change in serum TRAb from baseline to 2, 4, 6, 12 and 24 weeks
	To determine the optimal dose (or dose range) of daratumumab for patients with Graves’ disease	Dose–response curve for daratumumab against change in serum TRAb from baseline to 6 and 12 weeks
	To determine if daratumumab reduces thyroid hormone levels	Change in serum FT3 and FT4 from baseline to 2, 4, 6, 12 and 24 weeks
	To determine if daratumumab changes the time course of serum TSH	Change in serum TSH from baseline to 2, 4, 6, 12 and 24 weeks
	To determine if daratumumab changes thyroid size	Change in thyroid volume from baseline to 24 weeks measured by ultrasound
	To determine if daratumumab changes other thyroid autoantibodies	Change in serum ATPO and thyroglobulin antibodies from baseline to 6, 12 and 24 weeks
	To determine if daratumumab improves thyroid eye disease	Change in CAS, composite eye index and GOQoL score from baseline to 6, 12 and 24 weeks
	To determine if daratumumab improves thyroid symptom-related QoL	Change in ThyPRO39 score from baseline to 6, 12 and 24 weeks
	To determine if daratumumab is safe in this patient group	Change in serum immunoglobulins, specific antibodies including (SARS-CoV-2) and blood count parameters from baseline to 6, 12 and 24 weeks Adverse reactions to 24 weeks
Experimental	To determine if daratumumab changes lymphocyte/plasma cell transcriptomic markers	Analysis of blood plasma cell markers and mRNA signature
	To determine if daratumumab changes the lymphocyte subsets	Change in lymphocyte subsets (by FACS) from baseline to 6, 12 and 24 weeks

ATPO, antithyroid peroxidase; CAS, Clinical Activity Score; FACS, fluorescent-activated cell sorting; GOQoL, Graves’ Orbitopathy Quality of Life Instrument; QoL, quality of life; ThyPRO39, Thyroid Patient-Reported Outcome; TRAb, TSH receptor antibodies; TSH, thyroid-stimulating hormone.

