### Assessments

Follow-up visits will take place at weeks 4, 6, 12 and 24 (±1 week); the details of assessments are provided in table 4. At each visit, concomitant medications will be recorded, an AE check will be performed, compliance with antithyroid medication checked and FBC and thyroid function (TSH, FT4, FT3 and TRAb) will be assessed. Other assessments include goitre size assessment, eye examination, patient-reported quality of life measures (Graves’ Orbitopathy Quality of Life Instrument^4^ and Thyroid Patient-Reported Outcome^19^), specific antibody tests and other safety bloods (FBC, LFT). At the end of their participation in the trial, participants will be asked their opinion on which treatment allocation they received, and if they would recommend their treatment to a friend with the same condition. In addition, we plan to undertake exploratory analyses of lymphocyte subsets determined by flow cytometry and transcriptomic markers of plasma cells using quantitative reverse transcription-PCR.^20^

**Table 4 T4:** *S*chedule of assessments

Assessment/activity	Visit 1	Visits 2 & 3	Visit 4	Visit 5	Visit 6	Visit 7	Visit 8	Visit 9
			Day 0	Day 14 (±3 days)	4 weeks (±1 week)	6 weeks (±1 week)	12 weeks (±1 week)	24 weeks (±1 week)
Written informed consent	X							
Demographics & medical history	X							
Physical examination	X							
12-lead ECG	X							
Eye examination (CAS)	X							
Hepatitis B & C serology, HIV	X							
Bone chemistry	X							
Coombs, blood group, RBC phenotyping	X							
Pregnancy testing (females)	X						X	
COVID-19 vaccination offered		X X						
IMP infusion			X	X				
Weight	X	X	X	X	X	X	X	X
Resting pulse rate	X		X	X	X	X	X	X
Goitre size assessment	X		X			X	X	X
FBC	X		X	X	X	X	X	X
TSH, FT4, FT3, TRAb	X		X	X	X	X	X	X
U&E, LFT	X		X	X	X	X		
IgGAM	X		X			X	X	X
Height			X					
Eye examination (composite eye index)			X			X	X	X
Thyroid volume on USS			X					X
QoL questionnaires (GOQoL, ThyPRO)			X			X	X	X
TgAb, ATPO			X			X	X	X
Specific antibodies			X				X	X
Exploratory analysis sample			X			X	X	X
Vital signs			X	X				
Compliance with ATD			X	X	X	X	X	X
Concomitant medication		X	X	X	X	X	X	X
Adverse event reporting		X	X	X	X	X	X	X
Follow-up phone call			X	X				
End of trial questions								X

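### Table 1 promises change in CAS at weeks 6, 12 and 24, but Table 4 schedules CAS only at screening, so the two tables must be reconciled

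*Protocol article*

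**What the plan says.** Protocol article, Objectives, Table 1: improvement in thyroid eye disease is a secondary objective with three measures, given as "Change in CAS, composite eye index and GOQoL score from baseline to 6, 12 and 24 weeks". CAS and the composite eye index are listed as different measures.

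Protocol article, Assessments: the text refers the reader to Table 4 for timing: "Follow-up visits will take place at weeks 4, 6, 12 and 24 (±1 week); the details of assessments are provided in table 4". The narrative describes the rest in general terms: "Other assessments include goitre size assessment, eye examination, patient-reported quality of life measures". It does not name CAS and gives no visit for the eye examination.

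Table 4 has two eye rows. The row beginning "Eye examination (CAS" has one mark, at Visit 1. The row beginning "Eye examination (composite eye index" is marked at Visits 4, 7, 8 and 9, which are day 0 and weeks 6, 12 and 24.

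For safety, Table 1 also promises change in "specific antibodies including (SARS-CoV-2) and blood count parameters from baseline to 6, 12 and 24 weeks". In Table 4 the row "Specific antibodies" is marked at Visits 4, 8 and 9, which are day 0, week 12 and week 24.

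**The concern.** A change score needs a baseline and a follow-up value. A site that follows Table 4 exactly records CAS once, before treatment, and never again. One of the three measures named for the eye objective would then have no follow-up data in any participant.

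This matters because a CAS of 3 or more is one of the alternative entry routes in the inclusion criteria. It is how the article itself defines inflammatory eye disease. An analysis plan cannot supply measurements that were never scheduled, so the discrepancy has to be settled in the schedule or in the list of outcomes.

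The specific-antibody mismatch is smaller and belongs to a different objective. Only the week 6 value is unscheduled; the values at weeks 12 and 24 are in place.

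**Working it through.** No sample size, power or error-rate figure is involved. The check sets each time point promised in Table 1 against the visit columns of Table 4.

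**Visit key (Table 4).** Visit 1 = screening; Visits 2 and 3 = vaccination offered; Visit 4 = day 0; Visit 5 = day 14; Visit 6 = week 4; Visit 7 = week 6; Visit 8 = week 12; Visit 9 = week 24.

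| Measure | Follow-up promised in Table 1 | Marked in Table 4 | Day 0 value | Follow-up points scheduled |
|---|---|---|---|---|
| CAS | Weeks 6, 12, 24 | Visit 1 | No | 0 of 3 |
| Composite eye index | Weeks 6, 12, 24 | Visits 4, 7, 8, 9 | Yes | 3 of 3 |
| GOQoL (row beginning "QoL questionnaires (GOQoL, ThyPRO") | Weeks 6, 12, 24 | Visits 4, 7, 8, 9 | Yes | 3 of 3 |
| Specific antibodies | Weeks 6, 12, 24 | Visits 4, 8, 9 | Yes | 2 of 3 |

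**Eye objective as a whole.** Three measures at three time points make 3 × 3 = 9 planned follow-up values per participant. The schedule provides 0 + 3 + 3 = 6. The missing three are all CAS.

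**Is this a fault of text extraction?** It does not look like one. The CAS mark sits in the first visit column, as do the other screening-only rows around it. The specific-antibody row skips Visit 7, while the next row, for the exploratory sample, is marked at Visits 4, 7, 8 and 9. The other dated outcomes in Table 1 agree with Table 4: TRAb, FT3, FT4, TSH, ATPO and thyroglobulin antibodies, ThyPRO, immunoglobulins, blood count, thyroid volume and lymphocyte subsets (through the exploratory sample). The mismatches are confined to two rows.

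**Could the screening CAS serve as baseline?** Possibly, but the article does not name it as such. Visits 2 and 3 lie between screening and day 0. The section on consent and screening asks for a repeat pregnancy test when the interval exceeds 14 days, so a longer gap is expected in some participants. Even with screening as baseline, there is no follow-up value to subtract it from.

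**What can still be recovered?** The Trial status section says that stage 2 is underway. The interim analysis that precedes stage 2 needed 15 patients with 12-week data. If it ran as described, at least 15 of the planned 30 participants (15/30 = 50%) have passed the day 0, week 6 and week 12 visits.

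**The case against.** The strongest reply is that the screening row may exist only because CAS is an eligibility criterion, and that the later row labelled composite eye index may be a fuller examination in which the CAS items are also recorded. The article does not define the composite eye index. It condenses protocol V.6.0, which is not shown. On that view the fault is a label in a table, and the data exist.

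This part of the reply stands. A reader might infer that change in CAS cannot be computed at all, or that CAS was never collected after screening. The documents do not support that: they show only that no later CAS is scheduled in Table 4. Equally, they do not support the opposite assumption, because both tables treat CAS and the composite eye index as distinct and no sentence links them. Either way Table 4 needs correcting. Nor is this a detail left to the fuller protocol, since the article prints both tables and they conflict.

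A second reply is that little is lost. That also stands in part. Two of the three eye measures are fully scheduled, CAS is only one of several alternative entry routes, and an unknown share of participants will have active eye disease. A reader who concluded that the eye objective as a whole has failed would be going too far.

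**Conclusion.** The point holds as an internal inconsistency. As scheduled in Table 4, change in CAS has 0 of 3 promised follow-up values and no day 0 baseline. Specific antibodies have 2 of 3 follow-up values, which is a minor secondary point.

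The practical size depends on one fact that the article does not give: whether the eye examination at day 0 and weeks 6, 12 and 24 records the CAS items. If it does, the defect is one of documentation. If it does not, one named secondary measure has no follow-up data for completed visits, and those values cannot be obtained afterwards.

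The primary outcome, the power calculation, the interim rule, the composite eye index and GOQoL are untouched. The point deserves correction but does not threaten the trial's main conclusion.

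**What to change.** First establish whether the eye examination at day 0 and weeks 6, 12 and 24 already records the CAS items.

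- **If it does:** mark CAS in Table 4 at those four visits and state that the examination yields it. The cost is a table correction.
- **If it does not, and CAS change is kept:** add CAS to that examination for all remaining visits. Name the baseline (day 0, or screening where day 0 is missing). Report that CAS change is unavailable for visits already completed. The cost is a schedule amendment, case report form fields and a few minutes within an examination that already takes place. It does not repair the outcome for participants who have passed those visits.
- **If it does not, and CAS change is dropped:** remove it from Table 1 and document the reason. The eye objective then rests on the composite eye index and GOQoL.

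For specific antibodies, either add the assay to the blood already drawn at week 6 or delete week 6 from Table 1 for that outcome. The first costs one assay per remaining participant and cannot fill in past week 6 visits. The second costs a line of text.

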### Trial design

This is an adaptive, two-stage randomised phase IIa, single-centre clinical trial that will aim to recruit 30 patients with severe Graves’ disease from secondary care at the Newcastle upon Tyne Hospitals NHS Foundation Trust. It is a single-blinded trial in which participants will be blind to allocation. Recruitment start date: October 2021; planned end of trial (last patient last visit): April 2024.

Stage 1 is a dose–response study using four doses of daratumumab (9 mg/kg, 3 mg/kg, 1 mg/kg, 0.5 mg/kg) and a colourless, volume-matched placebo infusion in approximately 15 patients (ie, five groups of n=3, randomised in a 1:1:1:1:1 ratio using permuted random blocks without stratification) (figure 1).

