### Intervention

Each participant will receive two infusions, on day 0 and day 14 (±3 days). The prescribed daratumumab dose will be prepared in a 500 or 1000 mL bag of sodium chloride 0.9%, using the most recent available participant weight to calculate banded dose (see table 2 for volume and infusion rate). Each participant will be prescribed the same banded dose for both infusions, using the same weight for both. Where placebo is allocated, a volume-matched bag of sodium chloride 0.9% will be used. All participants will be pre-medicated with three non-IMPs, paracetamol (1 g orally), methylprednisolone (100 mg intravenously) and chlorphenamine (10 mg intravenously) at least 30 min prior to their allocated infusion.

**Table 2 T2:** Infusion rate table

Time (hour:min)	Rate (mL/hour)	Total volume at end of time (mL)
Stage 1 (1000 mL)		
1	80	80
2	160	240
3	240	480
4	320	800
4:40	320	1000
Stage 2 rate A (1000 mL)		
1	50	50
2	100	150
3	150	300
4	200	500
5	200	700
6	200	900
6:30	200	1000
Stage 2 rate B (500 mL)		
1	50	50
2	100	150
3	150	300
4	200	500

The maximum infusion rate of daratumumab was determined by the recommendation of the SmPC for daratumumab (DARZALEX 20 mg/mL concentrate for solution for infusion). For stage 1, all participants will receive the IMP/placebo diluted in 1000 mL sodium chloride 0.9% for both infusions. For stage 2, some patients may receive higher doses of daratumumab, so a more prolonged first infusion will be given to all participants. If participants have no IRRs during their first dose in stage 2, then the second dose may be given in 500 mL sodium chloride 0.9% with a faster infusion rate, in line with SmPC recommendations.

IMP, investigational medicinal product; IRRs, infusion-related reactions; SmPC, Summary of Product Characteristics.

Vital signs (pulse rate, blood pressure and temperature) will be recorded prior to the start of each infusion and every 15 min during the course of the infusion, and for 1 hour afterwards. Infusion-related reactions will be addressed as shown in table 3, and documented as an AE. Infusion charts will be completed to document compliance with prescribed dose. Participants will be followed up by phone approximately 2 days after each infusion visit to check for any AEs. After the day 14 visit, no further IMP will be administered. Patients will continue their regular medications, including antithyroid drugs and beta-blockers throughout the study, as deemed appropriate by the clinical team.

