### Safety reporting

AEs will be documented in patient medical notes before entry into the trial database. AEs judged by the investigator responsible for patient care as consistent with the usual clinical pattern for patients with severe Graves’ disease (eg, hyperthyroidism, hypothyroidism, tachycardia, bradycardia) will not be reported. Disease progression will be recorded as an AE only if it is more severe than expected in the trial population. AEs will be coded according to MedDRA classifications. All AEs meeting the criteria for seriousness will be reported by the investigator to the trial sponsor within 24 hours of awareness, and suspected unexpected serious adverse reactions will be reported to the Medicines and Healthcare products Regulatory Agency (MHRA) and Research Ethics Committee (REC) by the trial sponsor in line with regulatory reporting timelines.

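### The only clinical-event safety outcome in Table 1 counts adverse reactions, which depend on a causality judgement, while only participants are stated to be blind; all recorded adverse events by arm should be the outcome

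*Protocol article*

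**What the plan says.** In the Objectives section, the safety row of Table 1 has two parts. The first is laboratory-based: "Change in serum immunoglobulins, specific antibodies including (SARS-CoV-2) and blood count parameters from baseline to 6, 12 and 24 weeks". The second is the only outcome based on clinical events: "Adverse reactions to 24 weeks".

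On blinding, the Trial design section says: "It is a single-blinded trial in which participants will be blind to allocation". No other party is named as blind. The Randomisation section has members of the site research team performing randomisation.

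On the comparator, the Intervention section says: "Where placebo is allocated, a volume-matched bag of sodium chloride 0.9% will be used". It adds, for every arm: "All participants will be pre-medicated with three non-IMPs". It also says: "Infusion-related reactions will be addressed as shown in table 3, and documented as an AE".

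On collection, the Assessments section says that at each follow-up visit "concomitant medications will be recorded, an AE check will be performed". The Safety reporting section says: "AEs will be documented in patient medical notes before entry into the trial database". It adds that events are MedDRA-coded, and that events the investigator judges to fit the usual pattern of severe Graves' disease are not reported.

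**The concern.** An adverse event is anything untoward that happens. An adverse reaction is the subset that somebody attributes to treatment. The article keeps the terms apart: it uses AE for collection, coding and seriousness, and uses adverse reaction in the Table 1 outcome and in the standard regulatory term for suspected unexpected serious reactions. Table 1 therefore appears to make the clinical safety outcome depend on a causality judgement.

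Two things could follow.

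- **Differential attribution.** An assessor who knows that a patient received saline has less reason to call a later infection a reaction than if the patient had received daratumumab. A difference between arms, or between doses, could then reflect judgement and not event rates.
- **Missed harms.** The Risk assessment section says the main risk is a side-effect profile in benign disease that differs from the one seen in myeloma. An unfamiliar harm is the kind most easily judged unrelated, and an outcome filtered by attribution would leave it out.

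Safety and tolerability are among the stated purposes of stage 2, and safety information may override the model-based stage 2 doses. The listed outcome should therefore allow a fair comparison between arms.

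**Working it through.** The article states no figure for this outcome, so there is none to reproduce. The check has a textual part and an illustrative part.

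**1. What the text establishes**

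| Question | What the article gives |
|---|---|
| Which clinical events form the safety outcome? | Adverse reactions to 24 weeks (Table 1) |
| Is adverse reaction defined, or the causality assessor named? | No |
| Who is blind? | Participants only (Trial design) |
| What is the placebo? | Volume-matched saline, with the same premedication as the active arms (Intervention) |
| Are events recorded regardless of attribution? | Yes, except those judged typical of severe Graves' disease (Assessments, Safety reporting) |
| Which safety outcomes need no attribution? | Immunoglobulins, specific antibodies and blood counts (Table 1) |

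That the assessor knows the allocation is an inference from the single-blind description. It is the natural reading, but it is not stated.

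**2. Group sizes**

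Stage 1 has five groups of 3, so 3 patients on placebo. Stage 2 has 15 patients. With two doses and 1:1:1 allocation, 15/3 = 5 are on placebo. In total, 3 + 5 = 8 are on placebo and 30 − 8 = 22 on daratumumab. With one dose and 1:1 allocation, stage 2 adds 7 or 8 placebo patients, giving 10 or 11 in total.

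**3. Size of a spurious difference (illustration only)**

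Let the true event risk be p in both arms, and let the shares attributed to treatment be a1 on daratumumab and a0 on placebo. With no true effect:

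- spurious risk difference = p × (a1 − a0)
- probability of no adverse reaction among 8 placebo patients = (1 − p × a0)^8

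All three inputs are assumptions. For p = 0.4 and a1 = 0.5, the expected count on daratumumab is 22 × 0.4 × 0.5 = 4.4 of 22 (20%).

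| a0 | Expected on placebo, of 8 | Spurious difference | P(none on placebo) |
|---|---|---|---|
| 0 | 8 × 0.4 × 0 = 0 | 0.4 × 0.50 = 20 points | 1.00 |
| 0.25 | 8 × 0.4 × 0.25 = 0.8 | 0.4 × 0.25 = 10 points | 0.9^8 = 0.43 |
| 0.5 | 8 × 0.4 × 0.5 = 1.6 | 0.4 × 0 = 0 points | 0.8^8 = 0.17 |

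With a0 = 0, the lowest combination considered (p = 0.2, a1 = 0.3) gives 0.2 × 0.3 = 6 points. The highest (p = 0.6, a1 = 0.8) gives 0.6 × 0.8 = 48 points. The bias is zero whenever a1 = a0.

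**4. Missed harm (illustration only)**

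If 40% of daratumumab patients truly had the event and a quarter of those events were attributed, the outcome would show 0.40 × 0.25 = 10%. In counts, 22 × 0.40 = 8.8 patients would have the event and 2.2 would be counted.

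**The case against.** The case on the other side has real force.

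- **The placebo count is not fixed near zero.** A reader might infer that saline patients must score almost nothing. The documents do not support this. Every arm receives three premedication drugs and an infusion of 500 or 1000 mL. Infusion-related reactions are handled under the same Table 3 criteria in all arms and recorded as adverse events. A near-zero count needs a0 close to zero, which is an assumption. This objection stands.
- **Not every event type is affected.** A reader might also extend the concern to cytopenias and loss of immunity. These are captured by the laboratory outcomes in the same Table 1 row, which need no causality judgement. This stands too, and infection is the better example.
- **The interim decision is not tied to attributed reactions.** The Trial design section and the section on interim analyses speak of safety in general terms, and an independent monitoring committee meets at the interim. Nothing limits that review to the Table 1 item. This stands, so no claim can be made that the stage 2 dose decision rests on attributed reactions alone.
- **No formal comparison is specified for the safety row, and groups are small.** With about 8 placebo patients the assessment is descriptive in any case. This is fair, but a descriptive table by arm invites the same comparison and carries the same bias.
- **Tabulation details may sit in the full protocol or the SAP.** This is true of how causality is assessed and which adverse event tables are produced, and their absence from the article is not a fault. It does not answer the point, because the outcome itself is stated in the article, and an SAP that follows the outcome table would inherit it.

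**Conclusion.** The concern holds in a limited form. As written, the only clinical-event safety outcome ordinarily requires attribution to treatment, in a trial where only participants are stated to be blind and placebo is saline. It is therefore at risk of attribution bias between arms, and may miss unexpected harms that an investigator judges unrelated.

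Neither the size nor the direction can be established from the article. The illustrative spurious difference runs from zero, when attribution is equal across arms, to 48 percentage points at the most extreme combination considered, while low attribution would understate true harm. The conclusion rests on two readings: that adverse reaction carries its usual meaning, and that assessors may know the allocation. Neither is stated outright. Sample size, power and the primary outcome are unaffected. This should be changed, because the outcome is stated and the remedy costs little.

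**What to change.** In the safety row of Table 1, replace the adverse-reactions item with: *All recorded adverse events to 24 weeks, by MedDRA term, severity and seriousness, by randomised arm.* Keep investigator-attributed adverse reactions as a supporting tabulation.

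The change costs one line in Table 1 and the matching safety tables. No new data are needed, because events are already checked at follow-up visits, entered in the database and MedDRA-coded. The small downside is longer tables with more background events. The change does not recover events judged typical of severe Graves' disease, which Safety reporting excludes; the word *recorded* in the new outcome keeps that limit visible.
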